### Data collection

Data will be collected through face-to-face interview, at baseline and 6 months after enrolment (Table 2). Research assistants with the health and medical sciences background including lab assistants will be recruited and trained for a week on rapport building, research methods and debriefing of the survey tools. In order to ensure participants retention and follow-up, we will continue working closely with the community health workers, maintain regular follow-up phone calls with the participants, and engage peer supporters in respective study sites. A pre-testing of the survey questionnaires was conducted in the homogeneous non-sampling area and was revised as required. The final set of survey questionnaire was uploaded in the Kobotoolbox/ODK platform and data were collected using the ODK collect app in android tablets.

**Table 2 Tab2:**
[figure not shown]
Schedule for enrolment, baseline, intervention, and assessments

*m*, month

Study participants from each cluster will be invited to their local health facility for the data collection. A verbal and written informed consent will be obtained before the start of the interview. This was then followed by structured behavioural interview, anthropometric measurement, and lab test (blood glucose test). Data were collected by using different validated measurement tools based on the study outcomes that are presented in Table 1.

The random blood glucose level will be measured by glucometer at the baseline (HbA1c was taken by a sensitive POCT device by a trained Lab Assistant), and height and weight of the participants will be measured using the measurement tape and weighing machine respectively as part of anthropometric measurement. However, blood will not be stored for the future use in the ancillary studies. Weight will be assessed in the light clothing and barefoot to get the right value. Based on the height and the weight, the body mass index will be calculated dividing the weight (in kilogrammes) by height (in square metres). Waist circumference will also be taken using the STEPs guideline. Blood pressure was measured using appropriate measures for 3 times, the average of which was considered the final blood pressure. A set of validated standard tools was adopted to assess the secondary outcomes such as quality of life, healthcare utilization, and practice of self-care behaviours. Same process will be applied at the endline for the final data collection (Table 2).

### Safety and adherence considerations

The study participants enrolled in both the intervention and usual care arms will be briefed about the study, study purpose and their voluntary participation. A verbal and written consent form will be obtained from the study participants. The confidentiality of the participants will be maintained throughout the study. The proposed study is expected to cause no harm or effect to the study participants, however, if arises will be assessed by the project team members and determine whether any medical attention is required. Any complaints or feedback from the study participants will be recorded throughout the trial. In case of any serious complications raised during the trial, the participants will be seen by the doctor and can be asked to discontinue the trial if needed. The technical advisory committee (TAC) with the representation from the Ministry of Health and Population Studies, Nepal Health Research Council, World Health Organization Nepal, and Universities and Research Institutes in Nepal has been formed and responsible for overseeing the project implementation. This committee also function as trial steering committee (TSC). Kathmandu University, Nepal, is a project implementing organization which will be responsible for identifying potential participants, recruit them and obtain informed consents at the community and local health facility level. Furthermore, we have formed a Stakeholder and Public Involvement Group (SPIG) with the representation of different stakeholders and beneficiaries at community level. These involve the following: local municipal council, district education office, district health office, local health centre, female community health volunteer, mothers’ group, local sport clubs, and representative of consumer groups. We will closely work with the SPIG in order to ensure implementing the project activities smoothly at the community level. The research assistants with the health science background have been trained are being used for the data collection. Participants will be informed about the blood glucose test and the results of the test will be provided to the respective participants. Given this is a small community-based intervention trial and is not expected to involve any high risk or harm to the participants, the data monitoring committee (DMC) has not been established. For auditing, project management group will meet in every fortnightly and the ethical committee from Nepal Health Research Council (NHRC) will monitor in every 6 months. In the event of protocol amendments when required, the principal investigator will notify sponsor and funder and make necessary changes and updates to the trial registry and inform relevant ethical committees.

### Data analysis

#### Intention-to-treat analysis

The data analyses will follow according to the primary and secondary outcome measures between the intervention and usual care arms and at the end of the intervention against the baseline measures. Descriptive statistics will be calculated using mean (± SD) for the continuous variable and frequencies and percentages for the categorical variables. The primary outcome measure (mean HbA1c levels) at the end of 6-month intervention period will be compared between the intervention and usual care arms using generalized linear mixed models with a random cluster effect and adjusting for important baseline confounders. Analyses will follow an intention-to-treat approach including all clusters and participants in the group they are randomized to, regardless of whether they receive or complete the intervention.

Analyses of secondary outcomes will compare the proportion of participants who are adherent to lifestyle change (such as achieved moderate or vigorous physical activity, quit smoking, healthy diet, health care utilization, medication adherence, improved diabetes distress levels) at the end of the 6-month intervention period between the two intervention and usual care groups using generalized linear mixed models with a random cluster effect and adjusting for potential confounders. Variables proposed to interact with intervention will be tested (at *p* < 0.05) by including a cross product of each variable by the intervention in a model together with the main effects. A subgroup analysis will be performed by age, sex, SES, and residential status if there is any statistically significant interaction with the intervention, and the inferential analysis will follow cluster adjustment. In addition, the multiple imputation will be applied to handle the missing data.

An assessment whether any difference in outcome measures between usual care and intervention arms varies by HbA1c levels will be assessed using multi-variate analyses. The significance of subgroup effects will be assessed by tests of interactions of covariates and the intervention effect. We will also assess the differences in outcome measures by subgroups such as broadly classified as low, medium, or high intervention effect.

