## Introduction

Globally, type 2 diabetes mellitus (T2DM) accounts for 90–95% of all cases of diabetes and contributes to around 3% of total disability-adjusted life years (DALYs) [1–3]. The International Diabetes Federation (IDF) reported that 537 million adults were living with diabetes in 2021 and projected to reach 784 million by 2045 [4]; with global expenses around US$ 966 billion in 2021 and are projected to reach US$ 1054 billion by 2045 [4]. The IDF’s estimates indicate that more than 75% of people with diabetes live in low and middle-income countries (LMICs) [4]. Recent data suggest that the larger proportion of people with T2DM resides in South and Southeast Asian countries [4, 5]. In 2021, around 90 million adults (aged 20–79 years) were living with diabetes in the Southeast Asia region and 51.2% remained undiagnosed [4, 6]. T2DM imposes significant economic burden on patients, their families, health systems, and national economies, both directly due to treatment costs or indirectly because of loss of productivity [7].

Over the years, Nepal has been experiencing an increased burden of noncommunicable diseases (NCDs) including T2DM [8]. The prevalence of T2DM among adults in Nepal is estimated to be 8.5%, and a further 5.7% had raised blood glucose levels. A 2020 systematic review reported a pooled diabetes prevalence of 8.5% in Nepal [9]. Furthermore, a WHO Stepwise Surveillance (STEPS) survey reported 5.8% of adult Nepalese population in 2019 had raised blood glucose [10]. T2DM has represented a significant financial burden for Nepal, resulting in US$ 115.8 million in total diabetes-related health expenditure in 2021, and projected to reach US$ 190.5 million by 2045 [4]. Evidence also shows that the prevalence of T2DM risk factors is very high. For example, in 2019, the WHO STEP survey reported that around 24% of Nepalese were overweight and had raised blood pressure (BP), 17% had smoking behaviour, 11% had high cholesterol levels, 8% had insufficient levels of physical activity, 7% people consumed alcohol (highest 12% in the male), and 97% participants did not consume sufficient fruits and vegetables [10]. This suggests that the number of T2DM cases will continue to grow in the coming years.

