***Secondary outcomes***		
Quality of life	General	SF-8 [20], EQ-5D [21]
	Diabetes and oral health	Oral Health Impact Profile (OHIP-14) [22]
	Diabetes distress	Perceived Stress Scale (PSS) [23]
	Depression	PHQ-9 [24]
	Blood pressure	NDHS STEPS survey [14]
	Body mass index (BMI)	NDHS STEPS survey [14]
Program effectiveness (process evaluation)		Training for community health workers using Training of Trainers (TOT) modality for local capacity building, training for peer supporters focusing on facilitation and communication skills, monthly peer support meeting, follow-up
Healthcare utilization		Access to healthcare services Visit to health facility in last 6 months Specialist visits in last 6 months
Practice of self-care behaviours		24-h dietary recall and fruits and vegetable intake in a week adapted from SDSCA [15], NDHS STEPS survey for physical activity, MMAS-8 [16] for medication intake
Economic evaluation	Cost-estimation	No. of visits past 6 months to diabetes clinician/endocrinologist No. of visits past 6 months to other clinicians No. of visits past 6 months for emergency/acute care No. of overnight stays past 6 months in hospital (related to your diabetes)
	Cost-effectiveness analysis	Cost of healthcare resource use and EQ-5D
	Long-term economic impact analysis	Markov modelling

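### The only stated between-arm method for secondary outcomes compares proportions: it cuts the distress score to improved or not, uses a quit outcome defined only for smokers, and does not fit the other numeric scales

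*Protocol article*

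**What the plan says.** The Intention-to-treat analysis section gives one sentence on comparing secondary outcomes between arms: "Analyses of secondary outcomes will compare the proportion of participants who are adherent to lifestyle change". The examples are "such as achieved moderate or vigorous physical activity, quit smoking, healthy diet, health care utilization, medication adherence, improved diabetes distress levels", and the comparison is made "using generalized linear mixed models with a random cluster effect and adjusting for potential confounders". The baseline value of the outcome is not named as a covariate.

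Table 1 lists mostly numeric secondary measures. Diabetes distress is measured by the "Perceived Stress Scale (PSS"), oral health quality of life by the OHIP-14, depression by the PHQ-9, general quality of life by the SF-8 and EQ-5D, and medication intake by the MMAS-8, alongside blood pressure and BMI. The Data collection section says that the baseline procedures are repeated at endline.

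Two other statements bear on numeric outcomes. The analysis section says "Descriptive statistics will be calculated using mean (± SD) for the continuous variable", which is description and not a comparison of arms. Table 1 and the Economic evaluation section use EQ-5D in the cost-effectiveness analysis. No comparison of means or scores between arms is stated for any clinical or patient-reported secondary outcome.

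**The concern.** The same section compares the primary outcome as a mean and the secondary outcomes as proportions, so the text does distinguish the two. Three consequences follow.

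- **Distress and medication.** The phrase "medication adherence, improved diabetes distress levels" reduces PSS to improved or not, and implies a cut of MMAS-8. Improved or not depends on where a participant started, and it ignores the size of the change.
- **Smoking.** Only a baseline smoker can quit. Over all participants, never-smokers count as non-quitters. Over smokers alone, the comparison uses a subset, although the section promises to analyse everyone as randomised.
- **The remaining scales.** A proportion adherent to lifestyle change is not a natural summary of SF-8, OHIP-14, PHQ-9, BMI or blood pressure, so the stated method leaves them without a fitting comparison.

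The sample size is justified for HbA1c alone, so power lost on secondary scores is not made up elsewhere.

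**Working it through.** **1. The plan's own figure.** Inputs from Sample size: difference 0.5 (7.5% to 7.0%), SD 1.3, power 80%, 95% CI read as two-sided 5%, ICC 0.05, 15 clusters of 12 per arm.
- Individual n = 2 × [1.3 × (1.960 + 0.842) / 0.5]² = 106.1, so 107 per arm.
- Design effect = 1 + 11 × 0.05 = 1.55. Then 107 × 1.55 = 165.9 per arm, or 13.8 clusters of 12. Adding one cluster for small numbers gives 14.8, so 15 clusters and 15 × 12 = 180.
- A t-test on 28 df gives 80.8% power with 12 per cluster and 78.6% with 11, so 12 is indeed the minimum.
- Effective size per arm = 180 / 1.55 = 116. Standardised effect = 0.5 / 1.3 = 0.385.

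**2. Information kept when a normal score is cut, participant level.** Formula: φ(z)² / [p(1 − p)], with p the share beyond the cut. The article gives no cut-points, so p is assumed.

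| Split | Kept | Lost |
|---|---|---|
| 50/50 | 0.637 | 36% |
| 40/60 | 0.622 | 38% |
| 30/70 | 0.576 | 42% |
| 20/80 | 0.490 | 51% |

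**3. Allowing for clustering.** Cutting a score lowers its ICC. At the median, ICC = (2/π) × arcsin(0.05) = 0.032, so the design effect is 1 + 11 × 0.032 = 1.35. Information kept against an unadjusted endline score = 0.637 × 1.55 / 1.35 = 0.731, a loss of about 27%.

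**4. Against a baseline-adjusted score.** Adjustment multiplies the variance by 1 − r². The correlation r between baseline and endline is not in the documents; 0.3 to 0.7 is assumed. The cut outcome is taken without baseline adjustment, as the article names none.
- r = 0.3: 0.731 × 0.91 = 0.665, loss 34% (33.5% before rounding).
- r = 0.5: 0.731 × 0.75 = 0.548, loss 45%.
- r = 0.7: 0.731 × 0.51 = 0.373, loss 63%.

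If improved means any improvement from baseline, the share kept against the adjusted score is (2/π)(1 − r²) / [2(1 − r)] = 0.414, 0.477 and 0.541. The losses are 59%, 52% and 46% (participant level, equal ICC).

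**5. In power terms.** Take a secondary score with the primary outcome's standardised effect and 116 effective participants per arm (normal approximation).
- Unadjusted endline score: 83%.
- Cut at the usual-care median (50% against 65%): 64%, or 70% with the lower binary ICC (180 / 1.35 = 133 effective).
- Cut where the usual-care share is 20% (20% against 32.4%): 57.5%.
- Baseline-adjusted score: 87%, 92% and 98% for r = 0.3, 0.5 and 0.7.

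**6. Smoking.** The only prevalence in the article is the national survey figure, "17% had smoking behaviour". If it applied here, 0.17 × 180 = 30.6, so about 31 participants per arm could quit.

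**The case against.** A reader might infer that all the numeric outcomes in Table 1 will be dichotomised and that a third or more of their information is thereby thrown away. The text does not support that. The sentence is limited to adherence to lifestyle change, and its list is introduced as examples. SF-8, OHIP-14, PHQ-9, BMI and blood pressure are not in it. EQ-5D has a stated numeric use in the cost-effectiveness analysis. The named model family also covers continuous outcomes, since the same section applies it to mean HbA1c. All of this stands, and it confines the explicit dichotomising to distress and, by implication, medication adherence.

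It is also fair to say that cut-points, denominators and per-scale models are commonly left to an analysis plan, and one may exist. Their absence is not the point here. The point is that the one sentence the article does fix chooses proportions, and a later plan would have to depart from it to analyse the distress score as a score.

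The loss figures rest on assumptions. They need a roughly normal score that is actually cut, and they do not apply to smoking. The 27% against an unadjusted score is below a third, and part of the larger losses comes from adding baseline adjustment. The 17% describes Nepalese people in general, not people with diabetes aged 30 to 70 in these clusters.

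Finally, achieving a level of physical activity is a legitimate binary endpoint and should not be demoted.

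**Conclusion.** The concern holds in a limited form. The only between-arm method stated for secondary outcomes compares proportions. It expressly cuts the distress score, by implication cuts MMAS-8, and uses a quit outcome that exists only for baseline smokers. For the other numeric scales the fault is one of fit: the stated method does not suit them and no other is given.

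For a score that is cut, the participant-level loss is about 36% at a median split and 51% at 20/80. With clustering, a median split loses about 27% against an unadjusted score and about 34% to 63% against a baseline-adjusted one. These figures assume normality, the stated cut-points, an ICC of 0.05 carried over from HbA1c, and r between 0.3 and 0.7. The primary analysis is not affected.

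**What to change.** Amend the secondary-outcome sentence as follows.

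- Compare PSS, MMAS-8, SF-8, OHIP-14, PHQ-9, BMI and blood pressure as endline scores in a linear mixed model with a random intercept for cluster and the baseline value of the same measure. Report score differences with confidence intervals.
- Keep responder proportions for these scales as a supplement, with cut-points fixed before endline data are compared by arm.
- Replace quitting with current smoking at endline in all participants, adjusted for baseline smoking.
- Keep proportions for outcomes that are binary by nature, such as achieving moderate or vigorous activity.

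The cost is small: a wording change, the same data and the same software, with results read as score differences. Individual baseline and endline records must be linked, which the improved and quit outcomes already require. The Trial status section reports data collection in progress with endline planned for around mid-2023, so the change should be dated and made before any comparison by arm.

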### Sample size

The aim of this study is to assess the effectiveness of intervention in terms of reduction of mean HbA1c levels from 7.5% at baseline to 7.0% at 6 months follow-up among the intervention participants compared with estimated no or minimal changes in participants of usual care arm (HbA1c levels 7.5%), with at least 80% power and 95% confidence interval (CI) and assuming an intra-class correlation coefficient (ICC) of 0.050 and estimated HbA1c mean standard deviation (SD) of 1.3, as reported in studies that used diabetes self- management programs in the past [14]. The cluster RCTs implemented in similar settings of the Asian subcontinent in the past have used ICC of 0.02 [15] to 0.05 [16]. Allowing for cluster randomization with 15 clusters each arm, a minimum of 12 individuals would be required per cluster, equating to a total sample size of 180 per arm at 6 months follow-up. With the adjustment of possible maximum 15% attrition rate at 6-month follow-up, we required 211 participants in each arm at the baseline.

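### Exploratory subgroups graded by size of intervention effect are, as worded, defined by the outcome, so the comparison across them is circular

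*Protocol article*

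**What the plan says.** The Intention-to-treat analysis section sets out several layers of subgroup work.

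- Baseline-type subgroups, conditional on an interaction: "A subgroup analysis will be performed by age, sex, SES, and residential status if there is any statistically significant interaction with the intervention".
- A check on whether the arm difference "varies by HbA1c levels will be assessed using multi-variate analyses".
- A general rule for inference: "The significance of subgroup effects will be assessed by tests of interactions of covariates and the intervention effect".
- A further analysis, introduced as an addition: "We will also assess the differences in outcome measures by subgroups such as broadly classified as low, medium, or high intervention effect".

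The same section commits to the randomized comparison: "Analyses will follow an intention-to-treat approach including all clusters and participants in the group they are randomized to". On timing, the Data collection section says "Data will be collected through face-to-face interview, at baseline and 6 months after enrolment", so there is no intermediate outcome measurement.

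**The concern.** In the last of these analyses the grouping variable is the effect of the intervention and the quantity compared is the outcome. An individual's intervention effect is not observable. With one measurement before and one after, a participant or cluster can be graded on it only through the observed outcome or its change. Groups formed that way must differ in outcome, whatever the intervention does. They are also formed after randomization, so comparing them gives up the protection that the intention-to-treat rule is meant to provide.

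The danger is a published high-effect group made of measurement noise and ordinary within-person variation or, under another implementation, a real effect that disappears inside the strata.

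**Working it through.** **1. The plan's own figure.** The Sample size section aims at a "reduction of mean HbA1c levels from 7.5% at baseline to 7.0% at 6 months follow-up", a difference of 0.5 against unchanged usual care, with SD 1.3, ICC 0.05, 15 clusters of 12 per arm, 80% power and (read from the 95% CI) two-sided alpha 0.05.

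- Individually randomized: 2 × (1.960 + 0.842)² × 1.3² / 0.5² = 106.1, so 107 per arm.
- Design effect: 1 + 11 × 0.05 = 1.55. Then 107 × 1.55 = 165.9 per arm, or 13.8 clusters of 12; adding one cluster per arm gives 14.8, so 15.
- With 15 clusters per arm and a t test on 28 df, 12 per cluster gives 80.8% power and 11 gives 78.6%.
- Attrition: 180 / 0.85 = 211.8, against 211 stated.

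The sample size reproduces, so its inputs are used below.

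**2. Grading intervention participants by their own change, true effect zero.** The pre-post correlation r is not in the article; 0.3 to 0.8 is assumed.

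- SD of change = 1.3 × √(2(1 − r)).
- The mean of an outer tertile of a normal variable lies 3 × φ(z at 2/3) = 3 × 0.3636 = 1.091 SDs from the centre.

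This was checked by 1,000 simulated trials per setting (2 × 15 clusters × 12, normal data, no attrition), comparing each tertile with the whole usual-care arm.

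| r | SD of change | 1.091 × SD | Simulated high / medium / low effect |
|---|---|---|---|
| 0.3 | 1.54 | 1.68 | −1.67 / 0.00 / +1.66 |
| 0.5 | 1.30 | 1.42 | −1.42 / −0.01 / +1.41 |
| 0.7 | 1.01 | 1.10 | −1.09 / 0.00 / +1.09 |
| 0.8 | 0.82 | 0.90 | −0.89 / 0.00 / +0.89 |

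High and low groups differed at p < 0.05 in every null trial. With a uniform true effect of 0.5 and r = 0.5, the three groups show −1.92, −0.51 and +0.90: a low-effect group that appears harmed, although everyone benefits equally.

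**3. Grading intervention clusters by mean change, true effect zero.** Between-cluster variance is 0.05 × 1.69 = 0.0845; within-cluster variance is 1.6055. The mean of the top 5 of 15 normal values is about 1.03 SDs above the centre.

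- Cluster effects with the same correlation r over time: SD of cluster mean change = √[2(1 − r)(0.0845 + 1.6055/12)] = 0.55 at r = 0.3 and 0.30 at r = 0.8. Times 1.03 this is 0.57 and 0.30; the simulation gave −0.58/+0.57 and ±0.30.
- Cluster effects constant over time, so that they cancel (r then applies within clusters): SD = √[2(1 − r) × 1.6055/12] = 0.43 and 0.23. Times 1.03 this is 0.45 and 0.24.

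The range is therefore about ±0.24 to ±0.58.

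**4. Tertiles of change pooled over both arms, arms compared within tertile.** Under the null the within-tertile arm differences are about 0, and a group-by-arm interaction test (ordinary F test, clustering ignored) rejects in 4.6% to 6.1% of trials. With a true effect of 0.5, the arm differences within tertiles are about −0.14, −0.03 and −0.14, so most of the effect is absorbed by the grouping.

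**The case against.** The sentence is vague and names no way of forming the groups. It could mean exposure to the intervention, an effect predicted from covariates, or just a label for how large the effect turns out to be in the age, sex, socioeconomic and residential subgroups. The sentence before it puts subgroup inference on interaction tests. The analysis is exploratory and comes last in the section.

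Part of this stands. A reader might infer that the plan is bound to manufacture false responders. The article does not support that: the artefact in step 2 needs the intervention arm alone to be graded and set against usual care, and no such contrast is described. With pooled tertiles the harm is masking instead.

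The alternative readings do not rescue the wording. Exposure is also post-randomization. A covariate-predicted effect or a descriptive label is not what the text says, and the sentence is offered as an addition to the subgroups already listed. Nor is this detail that an article may leave to a fuller document: the analysis is stated, and as stated it is circular.

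A reader might also infer that testing whether the arm difference "varies by HbA1c levels will be assessed using multi-variate analyses" means stratifying on the 6-month value, which is the primary outcome. The article does not support that either. The section adjusts for baseline confounders and goes on to speak of covariates, so baseline HbA1c is the natural reading and only a qualifier is missing.

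**Conclusion.** Wrong as written, of moderate severity. Taken at its word, the sentence groups by the outcome and compares the outcome. Under a null intervention, participant grading against usual care gives about ±0.9 to ±1.7 HbA1c points, a high-to-low spread of 1.8 to 3.3, which exceeds the planned 0.5 throughout the assumed correlation range of 0.8 to 0.3. Cluster grading gives about ±0.24 to ±0.58, depending also on whether cluster effects persist. Pooled tertiles give no false differential effect but reduce a true 0.5 to 0.03–0.14. All figures assume normal data with SD 1.3 at both times, ICC 0.05 and 15 × 12 per arm.

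A stronger conclusion, that the trial's main result is compromised, does not follow. The primary mixed-model comparison, the sample size and the interaction tests on age, sex, socioeconomic and residential status do not depend on this sentence.

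**What to change.** Delete the sentence. Alternatively, define the strata from baseline variables only, for example baseline HbA1c and preferably kept continuous, and test them by an arm-by-covariate interaction in the cluster-adjusted mixed model already planned.

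As a clarification only, insert the word *baseline* before HbA1c in the statement on whether the arm difference varies by HbA1c level.

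An attendance-based complier-average analysis is not a suitable substitute. The Interventions section also provides telephone calls, mobile messages and a pictorial book, which may act on HbA1c without session attendance, and the Process evaluation section does not say that the session registry records individual attendance.

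The cost is wording only: no new data, no change in sample size and no change to the primary analysis. It should be settled before endline outcomes are examined by arm.
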